### Objectives {7}

Evaluate whether participants randomized to receive the intervention show increased media literacy, decreased body dissatisfaction, and/or improvements in secondary outcomes at timepoint 2 and timepoint 3 compared to baseline, relative to participants randomized to the control group.

Assess effects of moderators (socioeconomic status (SES), school type, geographical location) on any observed changes in primary and secondary outcomes in response to the intervention.

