### Outcomes {12}

All outcomes are self-report questionnaires and differences in scores will be compared from baseline (Timepoint 1), immediate post-test (Timepoint 2), and follow-up (Timepoint 3), as well as between intervention and waitlist control groups. All questionnaires will be administered at all three timepoints.

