### Participant timeline {13}

#### Sample size {14}

The trial aims to detect small between-group effects of our outcomes. The pilot trial in Colombia (*N* = 338) showed that the smallest effect size was approximately *d* = 0.3 (body dissatisfaction in boys); we aimed for a slightly lower effect size of *d* = 0.25. For the primary sample-size calculation, we assumed a two-sided significance level of *α* = 0.05, 80% power (1 − β = 0.80), and equal allocation to two arms (intervention vs. control), yielding 251 participants per arm. Because this trial uses a cluster-randomized design, sample size calculations incorporated clustering effects, including ICC (intraclass correlation coefficient) and DE (design effect), which determines how much the sample size needs to be inflated compared to an individually randomized trial). Based on the pilot trial in Colombia, we assumed an average group size of *m* = 25 and an ICC of 0.046, which requires 529 participants per arm. We allowed for 10% attrition, yielding a sample size of 611 participants and 1250 participants in total (see Table 1 and Fig. 1).

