## Statistical methods

### Statistical methods for primary and secondary outcomes {20a}

Data will be analysed using RStudio [30]. First, data will be assessed for completely missing at random using Little’s test (MCAR) [31]. If data is missing at random (MAR), we will employ linear mixed-effects models to examine the effects of the intervention, using the Maximum Likelihood approach. If data is not missing at random, we will employ Multiple Imputation. The number of imputations will be decided based on m≈ %missing (as recommended by [32]). Furthermore, we will run MNAR sensitivity analyses (pattern-mixture/delta) [33].

Each outcome will be analysed using a linear mixed-effects model including the baseline measure of the outcome, gender, and the interaction between gender (boys vs. girls) and group (intervention vs. control) as fixed effects, along with timepoint (baseline, immediate post-test, follow-up). Random intercepts will be included for participant (to account for repeated measures) and nested clustering of classes within schools to reflect the cluster-randomized design. Analyses will be conducted separately for each outcome variable; primary outcomes will be used for confirmatory inference, while secondary and exploratory outcomes will be analysed separately with appropriate multiple-comparison adjustment as required. To estimate effect sizes, we will calculate partial eta squared. Following Cohen’s [34] guidelines, values of 0.01, 0.06, and 0.14 will be interpreted as small, medium, and large effects, respectively [34].

Subgroup analyses will be conducted based on baseline scores for each outcome variable, comparing participants with high versus low initial levels (categorized using median splits of baseline scores). In addition, moderator analyses will include interactions between each moderator and group to examine the potential influence of gender, socioeconomic status (high vs. low), location (urban vs. rural), and school type (state vs. private) on intervention effects.

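### If the group-by-timepoint term that the objective needs is added to the stated random intercepts, its standard errors are too small whenever schools or classes drift differently over time

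*Protocol article*

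**What the plan says.** Three parts of the protocol article bear on this.

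- **The question.** Objectives {7} asks about improvement "at timepoint 2 and timepoint 3 compared to baseline, relative to participants randomized to the control group". Outcomes {12} says much the same: "differences in scores will be compared from baseline (Timepoint 1), immediate post-test (Timepoint 2), and follow-up (Timepoint 3), as well as between intervention and waitlist". Both describe a group-by-time contrast.
- **The fixed effects.** Section {20a} lists the baseline score, gender, and "the interaction between gender (boys vs. girls) and group (intervention vs. control) as fixed effects, along with timepoint (baseline, immediate post-test, follow-up"). No group-by-timepoint term is listed. Baseline appears twice, as a covariate and as a level of timepoint.
- **The random effects.** The same paragraph says "Random intercepts will be included for participant (to account for repeated measures) and nested clustering of classes within schools to reflect the cluster-randomized design". It mentions no random effect for school or class by timepoint, no robust variance and no degrees-of-freedom method.

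Schools are the randomised unit, and {20a} reserves confirmatory inference for the two primary outcomes.

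**The concern.** A random intercept for school, class or pupil takes the same value at T1, T2 and T3. Subtract T1 from T3 and it disappears. A group-by-timepoint contrast in such a model therefore has a standard error built only from the pupil-by-time residual. The model assumes that, apart from treatment, every school and class would have changed by the same amount. This is a stronger null hypothesis than no intervention effect.

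That assumption is hard to take for granted here. Follow-up falls anywhere between 9 and 12 months, delivery takes 2 to 4 weeks according to each school's preference, questionnaires are completed in class, and recruitment runs from August 2025 to August 2027. Some school-specific or class-specific change is plausible. If it exists, intervals for the change contrast are too narrow, and a chance difference in how a handful of schools drifted could be read as an effect on a primary outcome.

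**Working it through.** **The plan's own clustering allowance.** With d = 0.25, two-sided alpha 0.05 and 80% power, n per arm = 2 × (1.960 + 0.842)² / 0.25² = 251.2, which agrees with "yielding 251 participants per arm". With m = 25, the design effect is 1 + 24 × 0.046 = 2.104, and 251 × 2.104 = 528.1, rounded up to the stated 529. So the sample size allows for clustering. The question is whether the test of change would.

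**Inputs for the change contrast.**

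- ICC = 0.046, from Sample size {14}, placed at school level (an assumption).
- M = pupils per school: not stated; 25 and 50 tried.
- r = within-pupil correlation, as the share of the non-school variance that is constant over time: not stated; 0.5 to 0.8 tried.
- CAC = cluster autocorrelation, the correlation of a school's effect between two timepoints: not stated; 0.8 to 1 tried.

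**Formulas** (total variance 1, balanced complete data).

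- School-by-time variance: s = ICC × (1 − CAC)
- Pupil-by-time residual variance: e = (1 − ICC) × (1 − r)
- Variance ignored by the intercept-only model, as a ratio: DE = 1 + (M − 1) × s / (s + e)
- Actual type I error of a nominal 5% test: 2 × [1 − Φ(1.96 / √DE)]

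**One case in full.** With M = 25, CAC = 0.9 and r = 0.6, s = 0.0046 and e = 0.954 × 0.4 = 0.3816. DE = 1 + 24 × 0.0046 / 0.3862 = 1.286, and 1.96 / √1.286 = 1.728, giving 8.4%.

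**Results** (range over r = 0.5 to 0.8).

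| CAC | 25 pupils per school | 50 pupils per school |
|---|---|---|
| 1 | 5.0% | 5.0% |
| 0.95 | 6.3-8.4% | 7.8-11.9% |
| 0.9 | 7.7-11.7% | 10.6-18.2% |
| 0.8 | 10.4-17.7% | 15.8-27.7% |

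**Check by simulation** (2000 runs per setting, classes of 25, cluster variance split equally between school and class, r = 0.6 and 0.75). For CAC 0.8 to 0.9, the intercept-only test rejected 8.9-15.6% with 50 schools of one class and 10.0-20.5% with 24 schools of two classes. At CAC = 1 it stayed at about 4-6%. A t-test on school mean changes stayed at about 4-6% in every setting.

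**Other readings of {20a}.**

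- *Time-averaged group effect, which is what the listed terms imply.* This is tested against school variance. Simulated with ML and a normal reference, it rejected about 6-8% with 24 to 50 schools and 9-11% with 12. The excess is also there at CAC = 1, so it mainly reflects few clusters, not the mechanism described here.
- *T2 and T3 as responses, baseline as covariate only, random intercepts only.* The T3 effect then keeps part of the school variance. Simulation with a same-pupil correlation of 0.6 gave 5.5-9.1% for that effect.

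**The case against.** The strongest reply is that the inflated test is not one the protocol lists. Section {20a} contains no group-by-timepoint term, and the group effect it does imply is measured against school variance. A reader might infer that the primary analysis as written has a false-positive rate of 10-30%. The document does not support that: such figures belong to a model that the reader has completed, at chosen values of CAC, within-pupil correlation and school size, none of which is given. On the reading where baseline serves only as a covariate, the inflation is much milder. All of this stands.

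It is also fair to say that the text does not call the random intercepts the only random terms, that a fuller analysis plan may add covariance structure and degrees of freedom, and that the ICC is paired with a group size of 25, so it may be partly a class-level figure. The last point weakens the larger-school column but does not remove the effect: inflation remained when half the cluster variance was moved to class level.

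What does not stand is the idea that the listed model makes the point moot. It escapes the fault by not estimating the effect that Objectives {7} asks for. Repairing the fixed effects alone would bring the fault in, and changing from ML to REML would not remove it.

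**Conclusion.** The point holds in a conditional form and should be fixed. The stated random structure does not suit the objective's change-from-baseline contrast. Once that contrast is fitted, its standard error is too small unless schools and classes all drift alike. The type I error starts at 5% (CAC = 1). With the ICC of 0.046 at school level, r of 0.5 to 0.8 and 25 pupils per school, it is about 6-8% at CAC 0.95, 8-12% at 0.9 and 10-18% at 0.8; with 50 per school, about 8-12%, 11-18% and 16-28%. These figures rest on balanced, complete data. They show sensitivity to unstated inputs and are not an estimate of the error rate in this trial.

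**What to change.** In {20a}, name the group effects at T2 and at T3 as the confirmatory contrasts for each primary outcome. Then choose one of two structures:

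1. Analyse T2 and T3 each in a baseline-adjusted model with random intercepts for school and class, using school-based (small-sample) degrees of freedom. A version with school as the only cluster level held 4.9-5.5% in simulation for T3.
2. Keep the repeated-measures model, include group by timepoint, and add school-by-timepoint and class-by-timepoint random effects, with the same kind of degrees of freedom. This exact model was not simulated; the school-level test of change, which carries the same school-by-time variance, held about 4-6%.

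Either option takes a sentence or two in the analysis section and no new data. The price is somewhat wider confidence intervals, and a variance component may be estimated at zero.

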**Methods:**

We will recruit 1250 adolescents in 7th–10th grade (aged 11–17 years) to participate in a two-arm, cluster-randomized, open-label, controlled superiority trial in Colombia. Participating schools will be recruited by the research team. Participants will be randomized at the school level (1:1). Randomization blocks stratified by socioeconomic status (high vs. low) and geographical area (rural vs. urban) will be used to assign schools to either: (a) a school-based, four-session group intervention delivered over 2–4 weeks by trained facilitators (*n* = 625) or (b) a waitlist control group that will receive the intervention only after follow-up (*n* = 625). Participants need to be aged 11–17 years old, attending a participating school and class in grades 7 to 10, have written parental consent, and give written assent to be eligible for participation in this study. Individuals who cannot understand spoken or written language, or who do not have parental consent to participate, will be excluded. Primary outcomes are media literacy and body dissatisfaction. Secondary outcomes include appearance comparison, thin ideal internalization, curvy ideal internalization (girls only), drive for muscularity (boys only), eating disorder symptoms, and general wellbeing. Additional exploratory outcomes include risky appearance-altering behaviours (girls only), colourism, and skin colour satisfaction. Furthermore, adverse outcomes will be recorded.

Outcome assessments will happen pre-intervention (baseline; Timepoint 1), 1-week post-intervention (immediate post-test; Timepoint 2), and 9–12 months post-intervention (follow-up; Timepoint 3).

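### Two confirmatory primary outcomes have no stated multiplicity rule: if success on either one is enough, familywise error is about 8–10%, not 5%

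*Protocol article*

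**What the plan says.** - **Primary outcomes.** The Abstract (Methods) states "Primary outcomes are media literacy and body dissatisfaction", and the section on primary outcome measures lists the same two.
- **Where adjustment applies.** Statistical methods {20a} has each outcome analysed separately and continues: "primary outcomes will be used for confirmatory inference, while secondary and exploratory outcomes will be analysed separately with appropriate multiple-comparison adjustment as required". It gives no alpha split, testing order or all-must-succeed rule for the two primaries.
- **Alpha in the sample size.** Sample size {14} says "we assumed a two-sided significance level of *α* = 0.05", with "80% power (1 − β = 0.80), and equal allocation to two arms (intervention vs. control), yielding 251 participants per arm". The target effect is given as "we aimed for a slightly lower effect size of *d* = 0.25".
- **Success and timing.** Objectives {7} asks whether the intervention group will "show increased media literacy, decreased body dissatisfaction, and/or improvements in secondary outcomes at timepoint 2 and timepoint 3". Here *and/or* joins the outcomes, secondary ones included, while *and* joins the timepoints. The hypothesis in the Abstract (Discussion) uses *and* for both outcomes and timepoints. No section names a primary timepoint.
- **Order of analyses.** Interim analyses {21b} has an analysis once all post-test data are in and a final analysis after follow-up. Post-test results may be shown at conferences before then.

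**The concern.** The two primary outcomes are the claims for which the trial will be cited. They are also the only outcomes for which the plan mentions no adjustment. If a significant result on either one would be reported as a positive trial, two chances at 0.05 have been taken and the 5% error rate implied by the sample size does not hold. A second post-baseline timepoint with equal standing can add further chances. If instead both outcomes must succeed, the error rate is safe, but the stated 80% no longer describes the chance that the trial succeeds. Either way, the objective, the testing rule and the sample size do not fit together until a success rule is stated. A rule chosen after the post-test results are known would carry little weight.

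**Working it through.** **Inputs from the protocol.** Two-sided α = 0.05, power 80%, d = 0.25, m = 25, ICC = 0.046 and 529 analysed per arm (Sample size {14}); 625 randomised per arm (Abstract); 10% attrition; two primary outcomes; two post-baseline timepoints.

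**Assumed, because the protocol gives no figure.** Correlation between the test statistics of 0 to 0.7 between outcomes and 0 to 0.8 between timepoints.

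**1. Reproduce the plan's figure.**
- n per arm = 2(1.960 + 0.842)² / 0.25² = 251.2, against the stated 251.
- Design effect = 1 + 24 × 0.046 = 2.104. Then 251 × 2.104 = 528.1, rounded up to 529. This agrees with "we assumed an average group size of *m* = 25 and an ICC of 0.046, which requires 529 participants per arm".
- The calculation is thus for one comparison at the full 0.05. (The further step to 611 is a separate matter and is not used here.)

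**2. Familywise error with every test at 0.05 and no true effect.** Rejections in either direction count, as in the plan's two-sided α. Ranges come from simulating correlated two-sided z tests, 1,000,000 draws per setting.

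| Success rule | If independent | Over the assumed correlations |
|---|---|---|
| Either outcome, one test each | 1 − 0.95² = 9.75% | 8.3–9.8% |
| Either outcome at either timepoint | 1 − 0.95⁴ = 18.5% | 12.8–18.5% |
| Either outcome, significant at both timepoints | 0.5% | 0.5–4.3% |
| Both outcomes, each at either timepoint | 1.0% | 0.6–3.5% |
| Both outcomes at both timepoints | under 0.1% | under 1% |

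The fourth row holds only when neither outcome has an effect. If one outcome truly responds, the error rate is that of two tests on the other, up to 9.75%. Requiring both outcomes with one test each keeps the error at or below 5% in every case.

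**3. Power if both primaries must succeed.** With 80% for each, joint power is 0.80 × 0.80 = 64% if the outcomes are independent, rising towards 80% as they become more correlated.

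**4. Power per outcome if alpha is controlled.** Power = Φ(0.25 × √(n_eff/2) − z), where n_eff = n/2.104. For 529 analysed, n_eff = 251.4 and the first term is 2.803. For 625 × 0.9 = 562.5 analysed, n_eff = 267.3 and the first term is 2.890.

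| α per test | z | 529 analysed per arm | 562 analysed per arm |
|---|---|---|---|
| 0.05 | 1.960 | 80% | 82% |
| 0.025 (two tests) | 2.241 | 71% | 74% |
| 0.0125 (four tests) | 2.498 | 62% | 65% |

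The lower rows apply to Bonferroni or to the first step of Holm. With a true effect of d = 0.25 on both outcomes, Holm's power per outcome over two tests lies between the 0.025 and 0.05 rows.

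**5. Size needed to keep 80% per outcome.**
- At 0.025: 305 per arm, × 2.104 gives 642, / 0.9 gives 714, so 1428 in total.
- At 0.0125: 357, then 752, then 836 per arm, so 1672 in total.

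The plan has 1250.

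**The case against.** The strongest reply is that the protocol never says one positive result is enough. The Abstract's hypothesis joins outcomes and timepoints by *and*. Read as a decision rule, that would make an undivided 0.05 harmless. It is worded as an expectation, however, and Objectives {7} joins the outcomes differently. This part of the reply shows that the rule is unsettled, not that error is controlled.

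A second reply is that this is a condensed article and an SAP may fix the procedure. The mechanics of a procedure could well be left there. But the article does not leave multiplicity open: it says which outcomes are adjusted and sizes the trial at full alpha. An SAP that split alpha would contradict the stated power.

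Two stronger readings are tempting, and the document does not support either:

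- **That the error rate simply is 15–19%.** This needs a rule that any one of four tests suffices, and no section states one. The Objectives join the timepoints by *and*, and the fixed effects listed in {20a} include no group-by-timepoint term. The upper end also assumes no correlation between two measurements on the same pupils, and with higher assumed correlations the figure falls to about 13%.
- **That gender-specific tests make eight confirmatory comparisons** (1 − 0.95⁸ = 33.7% if independent). The model does contain a gender-by-group interaction, but {20a} lists gender among the moderators and no objective claims a gender-specific primary effect.

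It is also fair to say that the post-test analysis is described as a check of data quality and safety, has no efficacy stopping rule, and is not to be published before follow-up is complete. Showing results early does not itself inflate type I error. It matters here only as the deadline for fixing the rule.

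**Conclusion.** The point holds in a limited form. Both primary outcomes are confirmatory, each is tested separately, the full 0.05 is used, and no multiplicity rule is stated for them. That is narrower than saying the plan has no multiplicity control at all.

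Under the *and/or* objective with one test per outcome, familywise error is about 8–10%, roughly twice nominal. The 13–18.5% band applies only if either timepoint also suffices, and it rests on assumed correlations. Error is held to 5% only under a joint success rule. With both outcomes required and one test each, that is guaranteed; the 80% in the sample size is then power per outcome, with 64% for joint success under independence. The protocol does not say which of these cases applies, and that needs correcting because it governs the trial's main conclusion.

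**What to change.** Amend {20a} before the post-test analysis described in {21b}:

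1. Name one primary timepoint, and name the overall group difference at that timepoint as the confirmatory contrast.
2. Test the two primary outcomes by Holm at familywise 0.05. If both timepoints are to be confirmatory, apply Holm over the four tests and include the model term that yields the timepoint-specific contrasts.
3. If the intention is that both primaries must succeed, say so instead. No alpha adjustment is then needed with one test per outcome.
4. State that gender-specific effects are moderator results.
5. Bring the wording of the objective and of the Abstract's hypothesis into line with the chosen rule.

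Restate the power in Sample size {14} to match. For 529–562 analysed per arm it is 71–74% per outcome at 0.025, or 62–65% at 0.0125. Under a both-must-succeed rule, give the joint power. These figures come before any gain from baseline adjustment.

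The change is to text only if the trial accepts stated power below its 80% target. Keeping 80% per outcome at the adjusted level would take about 1428 participants for two tests or 1672 for four, against the planned 1250.

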## Assignment of interventions: allocation

### Sequence generation {16a}

Random blocks will be used to assign participating schools according to their SES (high vs. low) and geographical area (rural vs. urban), resulting in three different blocks: rural/low SES; urban/high SES; urban/low SES. In each block, schools will be randomly assigned to either the intervention or treatment group. The allocation sequence will be determined using computer-generated random numbers from Researchrandomizer.org.

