### Methods for additional analyses (e.g. subgroup analyses) {20b}

Subgroup analyses will be conducted based on baseline scores for each outcome variable, comparing participants with high versus low initial levels. In addition, moderator analyses will examine the potential influence of socioeconomic status (high vs. low), geographical area (urban vs. rural), and school type (state vs. private) on intervention effects.

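### Median-split baseline subgroups discard information that a continuous interaction would keep, and the SES and location interactions need one joint model because there is no rural/high-SES block

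*Protocol article*

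**What the plan says.** Two sets of effect-modification analyses are planned in the protocol article.

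- **Baseline level.** Statistical methods {20a} plans subgroups on the baseline score of each outcome, high against low, "categorized using median splits of baseline scores". Additional analyses {20b} repeats the plan as "comparing participants with high versus low initial levels" without restating the cut. The main model in {20a} already carries the baseline score as a continuous term: it is a "linear mixed-effects model including the baseline measure of the outcome, gender, and the interaction between gender (boys vs. girls) and group". No baseline-by-group term is listed.
- **Moderators.** {20a} then states that "moderator analyses will include interactions between each moderator and group", for "gender, socioeconomic status (high vs. low), location (urban vs. rural), and school type (state vs. private) on intervention effects". Neither {20a} nor {20b} says whether these interactions share a model.

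Objectives {7} sets the second objective as "Assess effects of moderators (socioeconomic status (SES), school type, geographical location) on any observed changes in primary and secondary outcomes". Baseline level is not among the moderators named there. Sequence generation {16a} crosses SES with geographical area, "resulting in three different blocks: rural/low SES; urban/high SES; urban/low SES". The fourth combination, rural/high SES, does not occur, and the analysis sections do not mention the empty cell.

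**The concern.** A baseline score cut at its median treats a student just above the cut like one at the extreme, and the cut moves with the sample. If the question is whether the effect depends on where a student starts, the score itself answers it with more power and without an arbitrary boundary.

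On SES and location, every high-SES school is urban and every rural school is low-SES. An SES interaction fitted alone compares urban/high with a mixture of urban/low and rural/low. A location interaction fitted alone compares rural/low with a mixture of urban/high and urban/low. Part of a location difference could then be reported as SES moderation, and the reverse. Both are named in the second objective, so their labels matter.

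**Working it through.** **Design figures used.** The protocol gives no power or precision figure for these analyses. Sample size {14} gives *d* = 0.25, two-sided α = 0.05, 80% power, *m* = 25, ICC 0.046, 10% attrition and 1250 participants. The design effect is 1 + 24 × 0.046 = 2.104, and 251 × 2.104 = 528.1, rounded up to the stated 529 per arm. With 10% lost, 1250 × 0.9 = 1125 are analysed.

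**1. Median split.** Assumptions: normal baseline score, linear moderation.

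- The correlation of a normal score with its median-split indicator is √(2/π) = 0.798.
- Information kept on the interaction: 2/π = 0.637. To compensate, N would have to rise by 1/0.637 = 1.57.
- A continuous interaction with 80% power has expected z = 1.960 + 0.842 = 2.802. After the split it is 2.802 × 0.798 = 2.235, so power = Φ(2.235 − 1.960) = 0.61.
- Starting from 90%, power becomes 0.73; from 70%, 0.51.

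**2. SES and location fitted one at a time.** Let the intervention effect be *t* in urban/low, *t + s* in urban/high and *t + l* in rural/low. Let *a*, *b*, *c* be the shares of participants in urban/high, urban/low and rural/low. Then:

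- SES alone estimates *s* − *l* × *c*/(*b* + *c*).
- Location alone estimates *l* − *s* × *a*/(*a* + *b*).

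The protocol gives no block shares, so these are assumed:

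| Urban/high, urban/low, rural/low | SES alone | Location alone | SES–location correlation |
|---|---|---|---|
| equal thirds | *s* − 0.50*l* | *l* − 0.50*s* | −0.50 |
| 25%, 50%, 25% | *s* − 0.33*l* | *l* − 0.33*s* | −0.33 |
| 25%, 25%, 50% | *s* − 0.67*l* | *l* − 0.50*s* | −0.58 |
| 40%, 40%, 20% | *s* − 0.33*l* | *l* − 0.50*s* | −0.41 |
| 50%, 25%, 25% | *s* − 0.50*l* | *l* − 0.67*s* | −0.58 |
| 20%, 40%, 40% | *s* − 0.50*l* | *l* − 0.33*s* | −0.41 |

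Illustration: if *s* = 0 and *l* = 0.20 SD (assumed), the SES interaction fitted alone is −0.50 × 0.20 = −0.10 SD with equal blocks, and −0.07 to −0.13 over the table. With *l* = 0.10 these values halve.

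**3. Fitted jointly.** SES is then identified by urban/high against urban/low, and location by rural/low against urban/low. A simulation with equal blocks, independent observations, *s* = 0 and *l* = 0.20 (2000 runs) gave a mean SES interaction of −0.10 when fitted alone. The joint model gave 0.00 for SES and 0.20 for location.

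**4. Price of the joint fit.** The variance rises by 1/(1 − 0.50²) = 1.33 with equal blocks, and by 1.12 to 1.50 over the table. For an interaction of 0.25 with 1125 analysed:

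- Alone, one third against two thirds: SE = √[(4/1125) × (3 + 1.5) × 2.104] = 0.183, power 28%.
- Jointly, on the two relevant blocks (750 participants): SE = √[(4/750) × (2 + 2) × 2.104] = 0.212, power 22%.
- For comparison, the main effect of 0.25 has power 82%.

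These powers are approximate, because they borrow the design effect of the main comparison.

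**The case against.** The best defence is that these are secondary analyses, and that the wording in {20a} does not commit the trial to fitting moderators singly. An interaction between each moderator and group can be read as several terms in one model, and an article may leave that choice to the full analysis plan. This stands: the mixing of SES and location depends on how the models are fitted, and the protocol does not settle it. What remains is that three named blocks and two separate binary contrasts are both fixed in the text, with nothing to say that they must be taken together.

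The 2/π figure also has limits. The outcomes are bounded Likert averages, one is a single five-point item, and moderation need not be linear. The figure is a guide for the multi-item scores and does not apply to the single item.

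A reader might go further in three ways that the documents do not support:

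- *That the split weakens the second objective or the primary analysis.* Baseline level is not in the second objective, and the main model uses the baseline score unsplit.
- *That the missing block by itself confounds SES with location.* The overlap is partial, and a joint model separates the two under additivity. Only their combination cannot be estimated.
- *That regression to the mean biases the subgroup results.* Both arms are split on the same pre-intervention score, so it is expected equally in both and does not bias a between-arm contrast.

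**Conclusion.** The point holds as two modest improvements to non-primary analyses.

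The median split is stated outright and is the weaker method: about 36% of the information on the baseline-by-group interaction is lost, and 80% power becomes about 61%, given a roughly normal score and linear moderation.

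The SES and location point is conditional. If the interactions are fitted one at a time, each carries about half of the other with equal blocks, and 0.33 to 0.67 over the assumed shares. A location effect would therefore appear only in part as SES moderation, with opposite sign. If they are fitted together, this bias disappears under additivity. At 22% to 28% illustrative power for an interaction as large as the main-effect target, neither approach supports a firm conclusion on moderation. Label: cheap improvement.

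**What to change.** 1. In {20a} and {20b}, replace the median split with a continuous baseline-by-group interaction for each outcome. Report the intervention effect at chosen percentiles, for example the 10th, 50th and 90th, and check linearity.
2. In {20a} and {20b}, state that the SES-by-group and location-by-group interactions are fitted in one model. Equivalently, fit block (three levels) by group with two contrasts: urban/high against urban/low, and rural/low against urban/low.
3. Say that these are a within-urban SES contrast and a within-low-SES location contrast, that the SES-by-location combination cannot be estimated, and that the results are exploratory.
4. Say whether school type enters the same model. The protocol does not show how it overlaps with the blocks, so no size can be given for it here.

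The work is text and analysis script; no design or data collection changes. The costs are a linearity assumption for the baseline term, which the check addresses, and wider intervals for the mutually adjusted contrasts (variance up by about a third with equal blocks).
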